### The Intervention

All consenting families in the intervention group will receive DHVs and ELs delivering dental care advice by a team of two dental home visitors at 6-month intervals. This advice will include information regarding daily tooth brushing, simple diet advice to prevent caries, and information on the need for regular dental check-ups. The families will also be provided with information about the dental services available in their vicinity and how to access these services. The duration of each visit will be approximately 30 minutes. A personalized approach that avoids direct persuasion will be used, and the dental team will acknowledge the parents’ right to choose when providing feedback and advice about dental care [18].

### Control Group

The control group will receive ELs that will be delivered by hand at 6-month intervals for the 2-year study period by the dental home visitors.

### Study Measures

#### Outcome Measures

The primary outcome of this study is the incidence of new caries, measured by the number of children included in the study with new caries, over a period of 2 years. The difference in the number of children with new caries between the intervention and the control groups will be considered as the number of children prevented from developing caries.

The calculated cost of the DHVs used in the intervention will include staff salaries, telephone calls to make appointments, travelling allowances, and administrative costs. The ELs cost is estimated by using the market price to purchase leaflets, staff salaries, telephone calls, travelling allowances, and administration costs. The cost of preventing a child from developing caries will be calculated as the DHVs and ELs cost divided by the number of children prevented from new caries.

The secondary outcome of this study will be the improvement in OHRQoL over a period of 2 years. This is measured by the improvement in the early childhood oral health impact scale (ECOHIS) scores. The difference in the ECOHIS scores between the intervention and the control groups will be considered as the improvement in OHRQoL. The cost of improving the OHRQoL is calculated as the DHVs and ELs cost divided by the improvement in the ECOHIS scores.

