### Sample Size and Randomization

It is estimated that there will be a 5% of incidence of caries in the intervention group during the follow-up, compared with 20% in the control group. This is based on the findings of a study conducted in 2015 by Koh et al that reported a 4% of incidence of caries in the intervention group and 39% in the control group [11]. Using a statistical software, Epi info 7 (Center for Disease Control and Prevention, USA, 2015), a sample size calculation was conducted and a minimum sample of 176 subjects is needed to detect a 15% difference in incidence of caries, with a significance level of 95% and a power of 80% [16]. The researchers decided to aim for doubling the effective sample size to 300 subjects to ensure the effective sample size will be higher than 176 with a high power. After taking sampling error into account and the assumption of a 30% nonresponse rate, followed by the assumption of another 30% of drop-out rate, a total of 600 subjects will be approached to participate in this study.

The kindergartens that agreed to participate will be randomly allocated into either the intervention or control group (1:1) by a random “draw” method. No matching will be done since they all have a similar socioeconomic background. All children aged 5 or 6 years at the participating kindergartens, with parents’ consent to participate, will be included in the study [17].

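### The number of children prevented from caries is defined as a raw difference in counts between arms, so unequal arm sizes distort it and can create an effect where none exists

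*Protocol article*

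**What the plan says.** In the protocol article, Outcome Measures fixes three things in sequence.

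- The measure is a count: "The primary outcome of this study is the incidence of new caries, measured by the number of children included in the study with new caries".
- The effect is a subtraction of counts: "The difference in the number of children with new caries between the intervention and the control groups will be considered as" the number of children kept free of caries.
- The cost of preventing caries in one child is the cost of home visits and leaflets "divided by the number of children prevented from new caries".

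Sample Size and Randomization sets the arm sizes, but only at cluster level: "The kindergartens that agreed to participate will be randomly allocated into either the intervention or control group (1:1"). Every child of eligible age with parental consent then enters. Kindergartens are not matched, and no cap or balancing on the number of children is described. The same section expects 30% nonresponse and then 30% drop-out from 600 approached.

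That section plans the trial on proportions: "5% of incidence of caries in the intervention group during the follow-up, compared with 20% in the control group". Neither Data Analysis nor Cost-Effectiveness Analysis adds a per-arm denominator or a rescaling to the count difference.

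**The concern.** A difference in counts measures prevention only when the two groups counted are the same size. Here the 1:1 ratio applies to kindergartens, which can differ in enrolment and in consent. Loss to follow-up may also differ between arms, and a child not examined at two years cannot be counted as having new caries, so losing children lowers an arm's count.

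The count difference then mixes the effect of the visits with the relative size of the arms. A larger control arm makes the visits look effective even if they do nothing; a larger intervention arm hides a real effect or makes the visits look harmful. The same number is the divisor of the cost per child prevented, which answers the protocol's first specific objective, so the error passes directly into that figure.

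**Working it through.** **The plan's own figure.** The protocol states that "a minimum sample of 176 subjects is needed to detect a 15% difference in incidence of caries". Take risks of 5% and 20%, 80% power, and the stated 95% level read as two-sided alpha 0.05 (an assumption, since sidedness is not given). The two-proportion formula is

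n = [1.960 × √(2 × 0.125 × 0.875) + 0.842 × √(0.05 × 0.95 + 0.20 × 0.80)]² / 0.15² = 75.1 per arm.

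The continuity correction, (n/4) × [1 + √(1 + 4/(n × 0.15))]², gives 87.9, so 88 per arm and 176 in total. This matches exactly. The trial was therefore sized on a difference in proportions, while its outcome is defined as a difference in counts.

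**Inputs**

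- p_I = 0.05 and p_C = 0.20, from Sample Size and Randomization.
- Children examined at two years: 600 × 0.7 × 0.7 = 294, from the same section.
- The split of the 294 between arms: not given, so assumed and varied below.

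**Formulas**

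- Rule as written: D = n_C × p_C − n_I × p_I.
- Children prevented in the intervention arm: P = n_I × (p_C − p_I).
- Hence D = P + (n_C − n_I) × p_C. The last term is the error. It does not depend on the treatment effect and is zero only if n_C = n_I.
- For a given cost numerator, the cost per child prevented is P/D times its correct value.

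**Results with 5% and 20%**

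| Examined, intervention / control | D, as written | P | Error in number prevented | Cost per child, multiple of correct value |
|---|---|---|---|---|
| 147 / 147 | 29.4 − 7.35 = 22.05 | 22.05 | none | 1.00 |
| 134 / 160 | 32.0 − 6.7 = 25.3 | 20.1 | +26% | 0.79 |
| 160 / 134 | 26.8 − 8.0 = 18.8 | 24.0 | −22% | 1.28 |
| 124 / 170 | 34.0 − 6.2 = 27.8 | 18.6 | +49% | 0.67 |
| 170 / 124 | 24.8 − 8.5 = 16.3 | 25.5 | −36% | 1.56 |

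**Results with no effect (20% in both arms).** P is 0 at any split. D is 0.2 × (160 − 134) = 5.2 at 134/160 and 0.2 × (170 − 124) = 9.2 at 124/170. With the arms reversed it is −5.2 and −9.2.

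**Drop-out alone.** Suppose consent is equal, at 600 × 0.7 / 2 = 210 per arm. Suppose 40% are lost in the intervention arm and 20% in control, an assumed pair that averages the protocol's 30%. Then 126 and 168 are examined, and with no effect D = 0.2 × (168 − 126) = 8.4.

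**How likely such splits are.** The article gives neither the number nor the size of the kindergartens. Simulated allocation with half the kindergartens in each arm and log-normal sizes gives this range:

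| Kindergartens | Coefficient of variation of size | Split outside 45:55 | Split outside 40:60 |
|---|---|---|---|
| 20 | 0.3 | 13.5% | 0.3% |
| 10 | 0.5 | 52% | 19% |
| 6 | 0.7 | 71% | 46% |

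The 134/160 split is about 46:54 and the 124/170 split about 42:58.

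**The case against.** The best counter-reading is that the named outcome is incidence, a word the protocol uses elsewhere for proportions, so the count is loose shorthand in a condensed article. This does not hold. The sentence that names incidence also says how it is measured, by number of children; the next sentence subtracts those numbers, and the cost formula divides by the result. This is a stated rule, not a detail left to an analysis plan.

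Several narrower points do stand.

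- The t test and logistic regression in Data Analysis are separate from this rule. The error falls on the number prevented and the cost per child prevented.
- The ICER in Cost-Effectiveness Analysis is a different ratio, built on treatment costs, carious teeth and ECOHIS scores. It does not use this number.
- Drop-out of 30% does not itself unbalance the arms; it must differ between them, and the protocol does not say that it will.
- Because kindergartens are drawn at random, either arm may turn out larger. If consent and attrition do not differ by arm, the expected count difference under no effect is zero, and the error belongs to the split that happens to occur. It becomes systematic only with differential consent or loss. The trial is run once, however, and its one reported figure would carry the whole error of its own split.

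**Conclusion.** The definition is wrong as written. The number prevented is off by (control size − intervention size) × control risk, in either direction, and the cost per child prevented is wrong accordingly. Under the protocol's risks and 294 examined children, the error runs from −22% or +26% at a 160/134 split to −36% or +49% at 170/124. With no effect and 20% risk in both arms, 124/170 would still report 9.2 children prevented.

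These sizes rest on assumed splits, because no cluster sizes are given; the error vanishes with equal arms, which the design does not secure. The minimum sample size of 176 is unaffected. Since the rule defines the primary effect and the divisor for the first objective, it should be corrected before analysis.

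**What to change.** Reword the primary outcome and effect in Outcome Measures along these lines:

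- The primary outcome is the proportion of children examined at two years who have at least one new carious tooth.
- The effect is the control proportion minus the intervention proportion.
- If a number of children prevented is wanted, it is that difference multiplied by the number of intervention children examined.

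Then put the cost on the same basis: mean cost per child divided by the difference in proportions. Taken over the same intervention children, this equals their total cost divided by n_I × (p_C − p_I). Any incremental ratio should likewise use per-child means in both numerator and denominator, so that arm size cancels.

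The cost is a short rewording. Each child's arm, caries status and the cost data are already to be collected, so data collection, randomisation and sample size do not change.

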#### Number of New Carious Teeth

An oral examination will be conducted at baseline (before the start of the intervention) and at the end of the 2-year study period by researchers using the NOHPS protocol, which was based on the World Health Organization (WHO) recommendation published in 2013 [19]. The number of new decayed, missing (due to caries), and filled posterior deciduous teeth (dmft), as well as the number of decayed, missing (due to caries), and filled first permanent molars (DMFT) will be recorded. The dmft and DMFT caries assessment is chosen to ensure consistency with the assessment used by the OHD Ministry of Health Malaysia.

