#### Follow-Up 6-Monthly Visits

Follow-up visits will be made every 6 months at the 6th, 12th, 18th month of the study period to the homes of both the groups. The parents in intervention group will receive DHVs and ELs by the dental home visitors, while those in the control group will receive only ELs to be delivered by the dental home visitors. The researchers will check the dental visit diary from both groups at each 6-month visit.

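### Cost per child prevented does not put cost and effect on the same children, so the ratio can rise with drop-out alone, by up to about 43% at the planned 30%

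*Protocol article*

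**What the plan says.** **The ratio.** The Outcome Measures section of the protocol article gives cost per child prevented as "calculated as the DHVs and ELs cost divided by the number of children prevented from new caries". The denominator is a difference in counts between the two arms, not a difference in proportions. The cost items are salaries, telephone calls, travel and administration. The Costs of Dental Home Visits and Educational Leaflets section adds training and consent paperwork to administration.

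**When the effect is seen.** The section Number of New Carious Teeth fixes the timing: "An oral examination will be conducted at baseline (before the start of the intervention) and at the end of the 2-year study period". There is no examination in between.

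**When cost arises.** The Intervention section gives visits and leaflets to every consenting family in the intervention arm. Baseline Data describes a first home visit, and Follow-Up 6-Monthly Visits states: "Follow-up visits will be made every 6 months at the 6th, 12th, 18th month of the study period".

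**Retention.** Sample Size and Randomization allows for non-response, "followed by the assumption of another 30% of drop-out rate".

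No section says whether the cost of visits to families who later leave enters the numerator, or whether the count is scaled to the number enrolled.

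**The concern.** Cost builds up from the first visit. The effect is recorded once, at the end. A child lost before month 24 may already have cost several visits but can never be counted as prevented. The count therefore shrinks in proportion to the number examined, while a programme total does not shrink at the same rate. Equal arms and equal drop-out do not remove this.

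The ratio answers the first specific objective. If cost and effect cover different children, it partly measures how well the trial kept its families. Two trials of the same intervention with the same true effect could report different costs per child prevented because their retention differed.

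The rest of the analysis plan does not repair the formula. Data Analysis compares group means by t test without redefining the ratio. The incremental ratio in Cost-Effectiveness Analysis uses other quantities: dental treatment cost over carious teeth or ECOHIS scores.

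**Working it through.** **Inputs** (Sample Size and Randomization, unless noted)
- Incidence: "5% of incidence of caries in the intervention group during the follow-up, compared with 20% in the control group", a difference of 0.15.
- Minimum sample 176, power 80%; two-sided alpha of 0.05 assumed.
- Target: "doubling the effective sample size to 300 subjects".
- 600 approached, with "the assumption of a 30% nonresponse rate" and then 30% drop-out. Non-response precedes enrolment, so it generates no visit cost.
- Visits at months 0, 6, 12 and 18 (Baseline Data; Follow-Up 6-Monthly Visits). Counting all four as costed visits is an assumption.

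**Step 1: the plan's own figures.**
- Two proportions, pooled variance under the null: n = [1.96·√(2×0.125×0.875) + 0.842·√(0.05×0.95 + 0.20×0.80)]² / 0.15² ≈ 75.1, so 76 per arm (152 in total).
- With continuity correction: 88 per arm, 176 in total. The stated figure reproduces.
- Drop-out chain: 600 × 0.7 × 0.7 = 294, close to the target of 300.

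**Step 2: children per arm, arms equal.**
- Enrolled: 600 × 0.7 / 2 = 210.
- Examined at 24 months: 210 × 0.7 = 147.
- Drop-outs: 210 − 147 = 63.

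**Step 3: the denominator.**
- Among those examined: 147 × 0.15 = 22.05 prevented.
- Scaled to all enrolled, if drop-outs benefit as completers do: 210 × 0.15 = 31.5.

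**Step 4: total cost against a completers-only ratio.** Visits stand in for cost. Completers receive 147 × 4 = 588 visits, so the matched ratio is 588 / 22.05 = 26.7 visits per child prevented.

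| Drop-outs' visits counted | Total visits | Visits per child prevented | Change |
|---|---|---|---|
| none (completers only) | 588 | 26.7 | 0 |
| 1 each (leave after baseline) | 588 + 63 = 651 | 29.5 | +11% |
| 2.5 on average (exits spread evenly) | 588 + 157.5 = 745.5 | 33.8 | +27% |
| 4 each (leave after month 18) | 588 + 252 = 840 | 38.1 | +43% |

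**Step 5: total cost over the observed count, against the same cost over the enrolled-scale effect.** The factor is (22.05 + 63 × 0.15 × b) / 22.05, where b is the share of the full benefit that drop-outs keep.
- b = 1: 31.5 / 22.05 = 1.43, which is 1/0.7.
- b = 0.5: 26.775 / 22.05 = 1.21.
- b = 0: 1.00.
- b = 2.5/4 = 0.625 (benefit in proportion to visits, exits spread evenly): 27.956 / 22.05 = 1.27, agreeing with Step 4.

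**Step 6: sensitivity.**
- Full benefit with lower drop-out: 1/0.9 = 1.11 at 10%; 1/0.8 = 1.25 at 20%.
- Baseline visit not costed: completers receive 147 × 3 = 441 visits. Leaving after baseline adds nothing. Exits spread evenly (1.5 visits on average) add 63 × 1.5 = 94.5, and 94.5 / 441 = +21%. Leaving after month 18 adds 189 / 441 = +43%.

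**The case against.** **The numerator is inferred.** A reader might take the article to say that it divides the cost of every child visited by an effect seen only in completers. It does not say so. The Intervention section states who receives visits, not whose costs enter the ratio. The first objective is worded per child and Data Analysis compares means, so per-child costing on one set may be intended. This stands, and the point must be conditional. Still, totalling over all families is the more natural reading of a total cost over a count, and no section limits cost to completers.

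**Overstatement is not automatic.** A reader might conclude that DHVs will look less cost-effective than they are. That requires both that drop-outs' costs are counted and that drop-outs gain something. Visits to families who later leave are also real resource use under the societal perspective; if those families gain nothing, total cost over the observed count is not inflated. This also stands.

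**The size is uncertain.** It depends on when families leave and on whether the baseline visit is a costed visit, and both arms have a home contact then. Training and paperwork do not scale with visits, and 30% is a planning allowance. All true, so about 43% is an upper figure at that allowance, not a forecast.

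**It is detail for a fuller document.** How missing examinations are handled may well be left there. The ratio itself is stated here, however, and as stated it can move with retention. That part of the objection fails.

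**One edit also cures dependence on unequal arm sizes.** True. But the mechanism here operates with equal arms, so it is a further reason for that edit.

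**Conclusion.** The concern holds in conditional form. The Outcome Measures section divides a cost by a raw count that can include only children examined at 24 months, and does not place the two on the same children. If cost is totalled over all families visited and drop-outs share in the benefit, cost per child prevented rises with drop-out alone. At 30% drop-out the ceiling is a factor of 1/0.7 = 1.43. Evenly spread exits with benefit in proportion to visits give about 1.27, or about 1.21 if the baseline visit is not costed. The factor is 1.00 if only completers' costs are counted or drop-outs gain nothing.

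These figures assume equal arms, equal drop-out, the planned 20% and 5% incidences, and visits as a proxy for cost. The documents do not support the flat statement that the ratio is overstated. They support the statement that its value depends on an unstated choice and, under the natural reading, on retention.

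**What to change.** In Outcome Measures, define cost per child prevented as the between-arm difference in mean DHV and EL cost per child, divided by the between-arm difference in the proportion with new caries, both on the same stated set of children. Say openly that this makes the numerator incremental, since the control arm also incurs leaflet, staff and travel costs; it is a different quantity from the present total.

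Report it for two sets:
- all enrolled children, with missing 24-month caries status handled, for example by multiple imputation;
- children examined at 24 months.

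Share fixed items such as training and administration per enrolled child. Costs are estimated from average salaries and daily allowances, so they can be assigned to each visit made; the article does not describe collecting them per visit.

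**Cost of the change:** revised wording and a little more analysis, with no new data. The completer version leaves out real spending on drop-outs, which the all-enrolled version covers. The all-enrolled version rests on the assumptions made about missing caries status.

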Cost-effectiveness analysis (CEA) is widely used to inform decision-makers about the value of new health programs and interventions. CEA is the most commonly used technique for economic evaluation and it estimates the costs and effects of health interventions and sums up the results in a cost-effectiveness ratio [14].

Given the high prevalence of dental caries in Malaysia, and the availability of effective DHVs and ELs material to support oral health promotion, the rationale of this study is to identify effective and cost-effective behavioral interventions to promote oral health and reduce oral health disparities in the population [1,7,8,12,13]. Health behaviors and lifestyles can influence both the oral and general long-term health of the population which can have economic and social consequences [15]. Furthermore, this is the first reported study of DHVs in Malaysia and an economic evaluation in this area is needed to estimate the value of the outcomes received for the expenditures spent on this intervention.

The aim of this study is to evaluate the cost-effectiveness of DHVs and oral health information in the form of ELs in preventing new caries development in young children, compared to those receiving only ELs over a period of 2 years. The specific objectives are:

To determine the cost of DHVs and ELs for prevention of new caries per child compared to the cost for a child only receiving oral health information through ELs for prevention of new caries after a 2-year follow-up.To determine the cost of DHVs and ELs in improving the oral health-related quality of life (OHRQoL) for one child compared to the cost of only ELs in improving the OHRQoL for one child after a 2-year follow-up.To compare the cost of dental treatment incurred and all associated expenditures among children receiving DHVs and ELs and those receiving only ELs over 2 years.

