#### Costs of Dental Home Visits and Educational Leaflets

The DHVs cost data will include the cost of dental home visitors, telephone calls, administration costs, and travelling costs of dental home visitors. The costs of the dental home visitors will be calculated according to the average salary of a dental nurse; the costs of the telephone calls used to make appointments for DHVs will be estimated according to the fees of prepaid phone number; and the travelling costs of the dental home visitors will be estimated by the average travel allowance per day in the Selangor area. The administration cost will include the costs of paper, stationary, and photocopies used for the informed consent forms and letters to authorities, as well as the training cost for delivering intervention. As the ELs used in the study will be obtained from existing Ministry of Health leaflets which are most relevant to the study objectives, the ELs cost in this study will be estimated by using the market price for purchase of leaflets, staff salaries, telephone calls, travelling allowances, and administration costs.

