### Data Analysis

Data collected from each visit will be checked for completeness by the research team members before it is keyed into SPSS. All the outcomes measures will be analyzed using the SPSS Program. Descriptive statistics will be used to report new caries teeth, OHRQoL, cost of DHVs and ELs, and the incremental cost effectiveness ratio (ICER) at 6, 12, and 18 months, as well as at the end of the 2-year follow-up period. A *t* test will be used for comparison of means of those parameters between the two groups and over the period of study. Logistic regression analysis will be carried out to test the influence of individual characteristics and on the CEA of the intervention in preventing caries.

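### One unqualified programme cost is the numerator of both the caries ratio and the ECOHIS ratio; with mean scores it cannot serve both, and the ECOHIS formula does not fix the per-child cost of objective 2

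*Protocol article*

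**What the plan says.** All references are to the protocol article.

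- **Objective 2 (Introduction)** asks for the cost of "improving the oral health-related quality of life (OHRQoL) for one child", compared with leaflets only.
- **Outcome Measures, the numerator.** "The calculated cost of the DHVs used in the intervention will include staff salaries, telephone calls to make appointments, travelling allowances, and administrative costs". The leaflet cost is built from similar items plus the market price of leaflets. The section on costs of visits and leaflets adds shared administrative items, including "letters to authorities, as well as the training cost for delivering intervention". No section divides this cost by a number of children.
- **Outcome Measures, caries ratio.** The cost of preventing caries in a child is "calculated as the DHVs and ELs cost divided by the number of children prevented from new caries".
- **Outcome Measures, ECOHIS ratio.** "The difference in the ECOHIS scores between the intervention and the control groups will be considered as the improvement in OHRQoL", and then: "The cost of improving the OHRQoL is calculated as the DHVs and ELs cost divided by the improvement in the ECOHIS scores".
- **Data Analysis.** New carious teeth, OHRQoL, the cost of visits and leaflets, and the ICER are listed for description. A t test is then "used for comparison of means of those parameters between the two groups".
- **Control Group.** Controls also receive leaflets, delivered by hand every six months.
- **Cost-Effectiveness Analysis.** The ICER takes the between-group difference in dental treatment cost as numerator, and new carious teeth and ECOHIS scores as outcomes.

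**The concern.** The two ratios stand in neighbouring paragraphs and share a numerator, but their denominators are of different kinds. The number of children prevented from caries grows with the number of children in the trial. A difference in mean ECOHIS score does not. Whatever unit the cost is given, one of the two ratios then depends on trial size.

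At stake is the result for objective 2. An analyst who carries the caries numerator into the ECOHIS formula would report a figure that rises with enrolment although cost and benefit per child stay the same. Separately, setting the full programme cost against an effect measured relative to leaflet-receiving controls does not match the comparison that objective 2 names.

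**Working it through.** **Inputs from the protocol (Sample Size and Randomization).** Caries incidence 5% against 20%, a difference of 0.15; minimum sample 176; target 300; 30% nonresponse, then 30% drop-out; 600 approached; 1:1 allocation of kindergartens.

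**The plan's own figures.** The protocol gives no value for the ECOHIS ratio. Its sample size reproduces: two proportions, two-sided 0.05, 80% power, with continuity correction, gives 88 per arm, or 176 in total (76 per arm without the correction). The recruitment chain is close: 300/(0.7 × 0.7) = 612, against 600 stated.

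**Arm sizes.** 600 × 0.7 = 420 enrolled, or 210 per arm. 420 × 0.7 = 294 completers, or 147 per arm. Whole kindergartens are allocated, so actual arms may be unequal.

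**Assumed, not in the protocol.** Programme cost c = 100 units per child; mean ECOHIS difference d = 2 points, with a range of 1 to 4.

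**Reading A: the cost is an arm total, n × c.**
- Caries ratio: n·c/(n × 0.15) = c/0.15 = 666.67 at every n. It behaves properly.
- ECOHIS ratio: n·c/d. With n = 147: 147 × 100/2 = 7,350. With n = 210: 210 × 100/2 = 10,500. Doubling n doubles the result.

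**Reading B: the cost is a mean per child, c.**
- ECOHIS ratio: c/d = 100/2 = 50 per point at every n (100 at d = 1, 25 at d = 4).
- Caries ratio: c/(n × 0.15) = 7.58 at n = 88, 4.44 at n = 150 and 2.22 at n = 300. It now falls as the trial grows.

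With a mean score difference, neither reading makes both formulas sound. The quotient of the two ECOHIS results is (n·c/d)/(c/d) = n, so the inflation under Reading A is the arm size whatever c and d are.

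**Reading C: arm total over a difference of summed scores.** With equal arms this gives n·c/(n·d) = c/d, which is sound. With unequal arms it is not. Assumed means of 8 and 10 with 160 and 140 children give 140 × 10 − 160 × 8 = 120. With 150 in each arm the difference is 150 × 10 − 150 × 8 = 300.

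**Full or incremental cost.** If leaflets alone cost an assumed 40 units per child, the incremental ratio is (100 − 40)/2 = 30 per point, against 50 with the full cost. This gap remains under Reading B.

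**The case against.** The strongest reply is that the protocol never calls the cost an arm total. The sentence that shows ECOHIS scores compared as means also covers the cost of visits and leaflets, because that cost is in the list just before it. If the sentence makes the denominator a mean, it can make the numerator a mean too, and mean cost over mean difference has no inflation. Objective 2, with its reference to one child, points an analyst the same way.

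This reply stands in part. A per-child reading is live, and a sensible analyst may choose it. It does not settle the formula: the same words would then mean an arm total in one paragraph and a per-child mean in the next. The list is also loose evidence on units, since it includes the ICER, which is itself a ratio between groups.

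A second reply is that summed scores should not be dismissed for depending on arm sizes, because the caries count has the same weakness. That is fair. With 160 and 140 children the expected count difference is 140 × 0.20 − 160 × 0.05 = 20, against 150 × 0.20 − 150 × 0.05 = 22.5 with equal arms. Still, summed scores are not stated anywhere and do not fit a comparison of means.

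A third reply is that a condensed article may leave cost units to a fuller document. It may, but here the article states the formula itself.

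**Conclusion.** The point holds as a conflict within the stated formulas. One cost term without a unit is put over a count and over a score difference, and if scores are compared as means no single meaning of that term serves both.

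A reader might infer that the protocol commits to dividing a whole-arm budget by a mean score, so that its result will be 147 to 210 times too large and useless for comparison with other programmes. The document does not support that. The arm total is inferred from the caries ratio, and the inflation arises only if that total is carried over. The factor also assumes the planned response and drop-out rates and equal arms.

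The mismatch between a full programme cost and a difference from leaflet-receiving controls does not depend on which reading is taken. Its size cannot be given from the protocol, which states no costs.

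Severity is minor to moderate: it affects the secondary cost result and leaves the sample size and data collection untouched.

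**What to change.** In Outcome Measures, define the ECOHIS ratio as the between-arm difference in mean cost per child divided by the between-arm difference in mean ECOHIS improvement per child, reported as cost per point per child. Keep arm totals out of this ratio. State in the same place that the cost in the caries ratio is an arm total, or put that ratio on a per-child basis too, as cost difference per child over risk difference.

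Then reconcile the cost numerator with the ICER in the Cost-Effectiveness Analysis section, which uses dental treatment cost, so that the two sections do not give two different cost figures for the same ECOHIS outcome.

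This takes a few sentences in two sections. It needs no new data and no change to the design.
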